**Life tables**

We will report the lifetime risk of surgery using life tables, this is considered a more accurate method for lifetime risk in comparison with cumulative risk as it considers the competing risk of death in the population(11). This will be calculated with a 95% confidence interval. The lifetables method has been used to calculate the lifetime risk of diabetes(9, 10). To calculate lifetime risk via the lifetable method we need to find the incident rate, mortality rate of those that have had surgery and the mortality rate for those who have not had surgery in each 5-year epoch. This can be done using the following equations(9):

[figure not shown]

[figure not shown]

Where
[figure not shown]
 is all-cause mortality,
[figure not shown]
 is the age-specific morality rate for those who have had surgery,
[figure not shown]
 is the age-specific morality rates for those that have not had surgery, Relative risk (RR) is the age-specific relative risk of mortality for those who have had surgery and
[figure not shown]
 is the age-specific prevalence of surgery.

The incident and mortality rates can then be used to find out the probability that a patient will transition from the state of not having surgery to having surgery or death and from having surgery to death, this is shown in the following equations(9):

Probability of transitioning from no surgery to death:

[figure not shown]

Probability of transitioning from no surgery to surgery:

[figure not shown]

Probability of transitioning from surgery to death:

[figure not shown]

Where IR is the age-specific incident rate of surgery and L is a period of time (five years). This will allow us to calculate the probability that a person aged x who has not had surgery will have surgery before reaching age x+1 or will die without having surgery before reaching age x+1. This can be applied to a hypothetical cohort to estimate the number of individuals in the population undergoing surgery at each 5-year epoch.

**Cumulative risk**

Cumulative risk can be used to estimate the lifetime risk of having surgery. This is calculated using the following equation(11):

[figure not shown]

Where P is the cumulative risk until age
[figure not shown]
, C_x_ is the total number of surgeries in age group
[figure not shown]
 and n_x_ is the number of person-years of age group
[figure not shown]
. This is multiplied by 5 as 5-year epochs are used. This will be calculated with a 95% confidence interval.

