***Background and rationale***

Each year approximately 5.1 million people undergo surgery representing a large proportion of NHS activity(1). Complications arise in one in five surgical procedures, which leads to prolonged hospital stays and higher costs associated with surgery and staying in hospital(2). The 30-day mortality rate of surgery is 1%, but one-year mortality rates increase by two-fold if a patient experiences a complication within the first 30 days after surgery(1, 2). Currently it is unknown how many times the average person will have surgery during their lifetime and thus how much surgical healthcare resources the average person will use over their lifetime.

Lifetime risk is a measure of the risk of an event occurring throughout an average person’s lifetime. It is a measurement that is used commonly to calculate a patient’s risk of developing a certain disease, for example breast cancer or cardiovascular disease, but it has not been used to assess the risk of a patient undergoing any type of surgery during their lifetime(3, 4). Knowing a patient’s lifetime risk of undergoing surgery could potentially help public health strategists anticipate and plan for the future burden of surgery, potential complications and mortality. Ideally, to calculate the lifetime risk of a patient undergoing surgery we would use a cohort study to assess a population across their lifetime and investigate if and at what age participants undergo surgery and when the participants die. However, this has limited feasibility at a population level. Instead, we will use two validated methods to calculate the lifetime risk of surgery: life tables and cumulative risk.

The COVID-19 pandemic has changed how healthcare is delivered and led to large changes in resource allocation(5). The pandemic has had a clear impact on surgery and waiting lists. However, the magnitude of this has not yet been quantified(6). This unmeasured impact could have influenced the lifetime risk of undergoing surgery during the pandemic period. We will use COVID-19 as an exposure to investigate the impact it has had on the lifetime risk of surgery.

This study aims to measure the lifetime risk of undergoing surgery and report any change in the lifetime risk during the COVID-19 pandemic.

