***Statistical Analysis***

There are two validated methods to measure lifetime risk – life tables and cumulative risk. We will calculate the lifetime risk of surgery using both methods, with life table’s being the primary method.

We will report the total number of patients undergoing surgery, as defined using the OPCS-4 codes, in the time frame assessed. This data will be categorised by 5-year epochs. We will then divide the total number of patients undergoing surgery for each 5-year epoch by the total population in that 5-year epoch using population estimates from ONS data. This will give us the age-specific incidence rates of surgery per head of the population.

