**Appendix 2**

### *The Life Table Method*

We calculated lifetime risk for both men and women in a sex-differentiated fashion because the life table method does not allow combined analyses. The incident rate of surgery in person-years was calculated for each 5-year epoch. We calculated surgical mortality rate and the all-cause mortality rate in person-years for each 5-year epoch.

The probability of no longer being alive and surgery free was calculated using equation 1^4^:

$$\lambda_{i}=r_{i}+m_{i}-s_{i}$$

Where $r_{i}$ is the incident rate of surgery in person years, $m_{i}$ is the all-cause mortality rate and $s_{i}$ is the surgical mortality rate. The probability of being alive and without previous surgery at age i was calculated using equation 2^4^:

$$S_{0}(i)=exp[-5\sum_{x=5}^{i} \lambda_{i}]$$

This was multiplied by 5 due to 5-year epochs being used.

Lifetime risk at age *i* was then calculated using equation 3^4^:

$${l_{i}=S}_{0}(i)\times r_{i} \times\frac{1-exp(-{5(\lambda}_{i}))}{\lambda_{i}}$$

The lifetime risk for period *y* (e.g. from 0-90) is calculated using equation 4^4^:

$$LR(y)= \sum_{i=0}^{90} l_{i}(y)$$

*Cumulative Lifetime Incidence*

Cumulative incidence was also used to estimate the lifetime risk of surgery, it was possible to calculate the overall cumulative lifetime incidence of first and all surgery as this method does not rely on mortality rates so male and female data can be combined. We calculated this using equation 6^10^:

$$P=1-exp(-5\sum_{x=5}^{i} r_{i})$$

Where P was the cumulative incidence until age i and $r_{i}$ is the incidence rate in person-years. This was multiplied by 5 as we used 5-year epochs.

**Supplementary figure 1:** Men (blue line) compared to women (red line) cumulative lifetime incidence of first surgery based on the years 2016-19. Error bars are the 95% CIs.

**Supplementary figure 2:** Men (blue line) compared to women (red line) cumulative lifetime incidence of all surgery based on the years 2016-19. Error bars are the 95% CIs.

**Supplementary figure 3:** Pre-pandemic (blue line) compared to the pandemic (red line) lifetime risk of all surgery for men and women (Error bars are 95% CIs). The pre-pandemic period was based on data from 2016-19 and the pandemic period was based on data from 2020. This was calculated using the life table method.

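### The all-surgery lifetime risk treats repeat operations as first events, so it is biased upward and flattens near 100% at older ages

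*SAP*

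**What the plan says.** The SAP counts different things in different places.

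- **Statistical Analysis:** persons. "We will report the total number of patients undergoing surgery", and then "We will then divide the total number of patients undergoing surgery for each 5-year epoch by the total population" of the same age band. Sample table 2 also has a column for patients.
- **Cumulative risk:** operations. C_x "is the total number of surgeries in age group" x, and n_x "is the number of person-years of age group" x, with no restriction to people not yet operated on. The purpose is given as "Cumulative risk can be used to estimate the lifetime risk of having surgery".
- **Appendix 2, Cumulative Lifetime Incidence:** equation 6 is P = 1 − exp(−5Σr). The text says that "it was possible to calculate the overall cumulative lifetime incidence of first and all surgery".
- **Appendix 2, life table (equations 1–4):** S₀ is the chance of still being alive and not yet operated on. The caption of Supplementary figure 3 nevertheless reports a pre-pandemic against pandemic "lifetime risk of all surgery for men and women" from this method. Supplementary figure 4 gives the same contrast for first surgery.

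The SAP does not say what the all-surgery percentage estimates, and Appendix 2 does not restate the numerator of r for first or for all surgery.

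**The concern.** Both formulas turn the rate of a first event among people still at risk into a probability. A second or third operation cannot remove anyone from the not-yet-operated state, because that person has already left it. If repeats are in the numerator and all person-years in the denominator, 5Σr is the mean number of operations per person (ignoring death). The formula turns that mean into the chance of at least one operation only if operations follow a Poisson process with one common rate at each age.

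Surgery clusters in people: some have many operations and some have none. For a given mean, clustering lowers the share with at least one, so the formula overstates it.

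Two things are at stake. The primary objective is the population lifetime risk, and a percentage pressed against 100% says little about it. The secondary objective is the pandemic effect, and a saturated percentage responds weakly to a change in activity. The section on the impact of the pandemic does not say whether its tests apply to first or to all surgery.

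**Working it through.** The SAP states no lifetime risk, so there is no figure to reproduce. The check evaluates its formulas.

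**Inputs**
- Volume: 5.1 million people a year (SAP, Background and rationale). This counts people. A count of operations would be at least as high and would saturate at least as much.
- Horizon: 90 years (Appendix 2, equation 4).
- Assumed, because the SAP gives none: population 53–67 million, a rate that is flat over age, and the size of the pandemic fall.

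**1. Cumulative formula to age 90.** r = 5.1/N, H = 90r, P = 1 − exp(−H).

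| N (million) | r per year | H | P | P after 34% fall | Change (points) |
|---|---|---|---|---|---|
| 53 | 0.0962 | 8.66 | 99.98% | 99.67% | 0.3 |
| 56 | 0.0911 | 8.20 | 99.97% | 99.55% | 0.4 |
| 67 | 0.0761 | 6.85 | 99.89% | 98.91% | 1.0 |

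Over the same populations, a 30% fall moves P by 0.2–0.7 points and a 50% fall by 1.3–3.1 points.

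**2. Bias when people differ.** Let personal rates vary as a gamma distribution with shape k and the same mean. Then P(at least one) = 1 − (1 + H/k)^(−k). At H = 8.20:

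| k (assumed) | P(at least one) | Equation 6 |
|---|---|---|
| no variation | 99.97% | 99.97% |
| 2 | 96% | 99.97% |
| 1 | 89% | 99.97% |
| 0.5 | 76% | 99.97% |

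**3. Younger ages.** At age 20, H = 20r = 1.52–1.92. P is 78–85%, and 63–72% after a 34% fall, a change of 13–15 points. There is no saturation there.

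**4. Life table, equations 1–4, with all-surgery rates.** Assumed: mortality 0.00003·exp(0.097 × mid-band age), capped at 0.4; surgical mortality set to 0; S₀ taken at the start of each band. Average rates are 0.075 and 0.10. They are either flat, or rising with relative values 0.5, 0.6, 1, 2 and 1.8 at ages 0, 20, 45, 75 and 90, scaled to average 1.

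| Average rate | Age pattern | Before | After 30% fall | Change (points) |
|---|---|---|---|---|
| 0.075 | flat | 99.35% | 97.62% | 1.7 |
| 0.075 | rising | 97.98% | 94.92% | 3.1 |
| 0.10 | flat | 99.79% | 99.15% | 0.6 |
| 0.10 | rising | 99.09% | 97.56% | 1.5 |

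**5. Expected number instead.** At 56 million, H = 8.20 operations. A 30% fall gives 0.70 × 8.20 = 5.74, so the full 30% shows. Weighting by a common survival schedule rescales both values and, with a uniform fall, leaves the ratio at 0.70.

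**The case against.** Several points against the concern stand.

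- **The quantity has a meaning.** A reader might infer that the all-surgery percentage is not a probability of anything. That goes too far. It is the chance of at least one operation under a common-rate assumption. The fault is that the assumption is unstated and implausible.
- **The pandemic effect is not hidden.** A reader might infer that it is, or that the measure cannot respond. The documents do not support this. The captioned pandemic figures use the life table, which is the primary method and compresses less than equation 6. The captioned cumulative-incidence figures compare men with women in 2016–19 only. Supplementary figure 4 gives a first-surgery pandemic contrast, which counting repeats does not affect. Sample table 3 reports by age band, and younger ages move by many points.
- **The inputs are partly assumed.** Population, age pattern, mortality and the size of the fall are not in the SAP. The conclusion to age 90 holds across the ranges tried, but the exact values do not come from the SAP.
- **That all surgery counts every repeat is an inference.** The equation in the cumulative-risk section is not shown, and Appendix 2 does not restate the numerator. But the section's text names surgeries, and Appendix 2 contrasts all with first. Even a count of persons per year includes someone again in each later year of surgery, so the difficulty remains.
- **Lifetime risk is the stated objective.** The remark in the background that "Currently it is unknown how many times the average person will have surgery during their lifetime" is context. Failing to report a mean number of operations breaches no objective. It does show that this measure would be useful, and the same inputs supply it.

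**Conclusion.** The concern holds in a limited form. As written, the all-surgery lifetime risk applies a first-event formula to counts that include repeats, over all person-years, and in the life table this conflicts with the SAP's own definition of S₀. The result is biased upward: at H = 8.20 it gives 99.97%, where assumed gamma variation with shape 2, 1 or 0.5 gives 96%, 89% or 76%. To age 90, equation 6 gives 99.89–99.98% at the SAP's volume, and an assumed 34% fall shifts it by at most about 1 point. The life table shifts by about 0.6–3.1 points for an assumed 30% fall. Saturation is confined to older ages and to the all-surgery measure. The upward bias from clustering applies to that measure at any age. Separately, the numerators conflict: patients in Statistical Analysis and sample table 2, surgeries in Cumulative risk.

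**What to change.** 1. Report probabilities for first surgery only. Define r as first surgeries divided by surgery-free person-years. Changing the numerator to patients is not enough, because patients operated on in a period include people with earlier surgery. State how a first operation is recognised in the data.
2. For all surgery, replace the percentage by the expected number of operations per lifetime: the sum over age bands of r_x times the person-years lived in band x per birth, with survival from all-cause mortality. Give it by sex and period, with the pandemic effect as a ratio and its 95% confidence interval. State whether the ratio uses each period's own mortality or a common schedule.
3. Count operations for the second measure and first-surgery persons for the first, and bring Statistical Analysis, Cumulative risk and sample table 2 into line.
4. Say in the pandemic section which measure its tests apply to.

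Cost: the expected number uses inputs already planned and a simpler formula. Supplementary figures 2 and 3 must be redrawn and relabelled. The first-surgery measure is already reported, so its definition needs writing down, and its denominator needs recalculating if all person-years were used.

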***Impact of COVID-19 Pandemic***

We will consider COVID-19 as an exposure and calculate its impact on the lifetime risk of having surgery. The impact of the COVID-19 pandemic on the lifetime risk of surgery will be investigated by assessing for any difference in lifetime risk in the specified time-period for pre-pandemic and pandemic. We will do this by generating the five-year epochs for the pre-pandemic period and then for the pandemic period and comparing the two. To investigate for a significant statistical difference between the lifetime risk of surgery in the pre-pandemic period and the pandemic period we will use two methods. The first test will involve using 95% confidence intervals(12). If the 95% confidence intervals for the lifetime risk of surgery in the pre-pandemic period does not overlap with the 95% confidence intervals in the pandemic period or the 95% uncertainty interval for relative percentage change does not include 0 then there will be a statistically significant difference in the lifetime risk of surgery between the pre-pandemic and pandemic periods(12). The second test will be a T-test, a P-value 0.05 will be considered statistically significant.

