***Secondary Objective:***

1. To report the impact of the COVID-19 pandemic on the lifetime risk of surgery.
2. **Methods**

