***Study design and setting***

This is a nationwide observational cohort study that will describe the number of patients undergoing surgery in aged-specific 5-year intervals in the National Health Service (NHS) in England between 1^st^ April 2015 and 31^st^ August 2020_._ This will then be compared with data on population estimates from the ONS for each 5-year age interval to calculate lifetime risk. The impact of the COVID-19 pandemic on the lifetime risk of surgery will be assessed by comparing data from a pre-pandemic period defined as __ to the ____,_ to a pandemic period defined as __ to the ____._

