***Participants and data collection***

All patients, of any age, identified as undergoing surgery using HES-APC in England between 1^st^ April 2015 and 31^st^ August 2020 will be included. Surgery will be defined using the assigned Office of Population Census and Surveys Version 4 (OPCS-4) codes for hospital procedures. Surgical procedures will be identified by using a predetermined list of OPCS-4 codes(1). The number of patients undergoing surgery will be categorised into 5-year age bands. Population estimates will be found using national life tables released from the ONS, this again will be categorised into aged-specific 5-year age bands(8).

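### The planned pre-pandemic versus pandemic contrast measures lifetime risk if pandemic-period rates lasted for life; it is a valid period summary but should not be reported as the impact of COVID-19 on lifetime risk

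*SAP*

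**What the plan says.** The Secondary Objective is "To report the impact of the COVID-19 pandemic on the lifetime risk of surgery". The section Impact of COVID-19 Pandemic puts this in causal terms: "We will consider COVID-19 as an exposure and calculate its impact on the lifetime risk of having surgery". The method is a comparison of two complete sets of age bands: "We will do this by generating the five-year epochs for the pre-pandemic period and then for the pandemic period and comparing the two". Any difference is then tested for significance.

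The length of the exposure is poorly fixed. Study design and setting leaves the dates blank ("to a pandemic period defined as __ to the"). Participants and data collection limits the data to operations "between 1^st^ April 2015 and 31^st^ August 2020". In Appendix 2 the caption of Supplementary figure 3 says: "The pre-pandemic period was based on data from 2016-19 and the pandemic period was based on data from 2020".

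In the change log and Appendix 2, equation 2 multiplies the summed band rates by 5, equation 3 gives each band's contribution over five years, and equation 4 adds the contributions from age 0 to 90. The Life tables section refers to a hypothetical cohort. No section says that the pandemic result is conditional on pandemic rates continuing for life.

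**The concern.** A life table built from one period's rates describes a synthetic person who meets those rates at every age. For 2016-19 this is the usual reading of a period lifetime risk. For the pandemic period it describes a whole life at the rates of part of 2020, with no restart of services and no catch-up. Nobody in the data had that exposure. A real person met the pandemic rates for months, at one age.

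The Background also says that "The pandemic has had a clear impact on surgery and waiting lists", so some of the fall may be postponed surgery, and the extract closes before its later delivery could be seen.

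If the plan is followed as written, the secondary objective is answered with a quantity that does not match its wording. A reader could take a fall of many percentage points as the loss in people's lifetime chance of surgery caused by the pandemic.

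**Working it through.** The SAP states no rate, lifetime risk or expected difference, so there is no figure of its own to reproduce. The check compares what the equations compute with what the objective names.

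**Inputs from the SAP**
- Age span 0 to 90, each band's rate held for 5 years (equations 2 to 4).
- Data end 31 August 2020, so at most 8 months of 2020 are in the extract. The appendix's 2020 is at most 12 months.

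**Exposure time alone**
- 90 years ÷ 12 months = 90.
- 90 years ÷ 8 months = 90 ÷ (8/12) = 135.

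**Assumed inputs (not in the documents)**
- Surgery rate *r*: 2% a year at age 50, varied from 0.5% to 4%. It is multiplied by an age factor, interpolated between .6, .5, .5, .8, .9, 1.0, 1.5, 1.8, 1.6 and 1.2 at ages 0, 5, 15, 25, 35, 50, 65, 75, 85 and 95.
- Mortality *m* rising exponentially with age; surgical mortality *s* = 0.
- Fall in rates *f*: 35%, varied from 20% to 50%.
- Duration *d*: 5, 8 or 12 months, with six months obtained by scaling.

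**Formulas** (equations 1, 3 and 4, with survival counted from age 0, on a yearly grid to age 95)
- λ = r + m − s.
- Contribution at each age: S₀ × r × (1 − exp(−λ)) / λ, summed to give LR.
- Planned contrast: LR(r) − LR((1 − f)r), with the fall at every age.
- Duration-limited effect at age *a*: LR(r) − LR(r*), where r* equals r except in that one year of age, where it is r(1 − f·d), with d in years.

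**Results, 2% and a 35% fall**
- Planned contrast: 77.0% to 62.4%, a fall of 14.6 points. The five-year grid gives 76.8% at baseline, so the grid does not matter.
- Eight-month fall: at most 0.11 points from birth at any age; ratio about 128.
- Twelve-month fall: at most 0.17 points; ratio about 85.
- Six-month fall: the effect is close to proportional to duration, so 0.17 ÷ 2 ≈ 0.09 points; ratio about 2 × 85 = 170.

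For a version the reader can repeat, set m = 0.00003 × exp(0.095 × age), held between 0.0002 and 0.4. This gives 77.4% to 62.8%, again 14.6 points, against at most 0.086, 0.115 and 0.172 points for 6, 8 and 12 months.

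**Hand check.** A person cannot lose more than f × r × d. At the highest assumed rate, 1.8 × 2% = 3.6% a year, eight months gives 0.35 × 0.036 × 8/12 = 0.0084, or 0.84 points. This is before allowing for people already operated on, already dead, or operated on later. It is still far below 14.6.

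**Range.** Over all assumed rates, falls and durations of 5 to 12 months, the planned contrast from birth is 64 to 370 times the largest duration-limited effect.

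**Remaining risk at older ages.** For people still surgery-free when the fall occurs (2% base, falls of 20% and 50%), the twelve-month ratios, and twice these for six months, are:

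| Age | 12 months | 6 months |
| --- | --- | --- |
| 60 | 24.2 to 27.2 | 48 to 54 |
| 80 | 7.5 to 7.8 | 15 to 16 |
| 90 | 3.4 to 3.5 | about 7 |

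**The case against.** The best defence is that the SAP intends a period measure throughout. The Background aims to report change during the pandemic, the Life tables section speaks of a hypothetical cohort, and Derivation of variables repeats the calculation year by year. A period life table is a standard summary of current rates, and the ratios above compare two different quantities rather than expose a miscalculation. This stands: the computation is not wrong. It does not rescue the wording, because the Secondary Objective and the COVID-19 section name an exposure and its impact, and no condition is attached.

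Several further points also stand.
- The captions of Supplementary figures 3 and 4 and the columns of Sample table 3 name periods and do not say impact. What they lack is the condition.
- Sample table 2 already sets out patients and person-years by age band for two periods, so the rate comparison is partly planned.
- All sizes rest on assumed rates for a single event, whereas Supplementary figure 3 concerns all surgery.
- A reader might take the duration-limited result as an upper bound on the true loss. The documents do not support that: data stop on 31 August 2020, and nothing shows that rates had recovered by then.
- A reader might also infer that planners will be told that need has fallen. The SAP does not say so; it counts surgery delivered, and it mentions waiting lists itself.

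**Conclusion.** The point holds as one of estimand and labelling. The planned contrast answers what lifetime risk would be if pandemic-period rates persisted for life. It does not answer what the pandemic did to lifetime risk.

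That the planned contrast is the larger needs only that the fall is temporary. Its size depends on the assumptions: over 100-fold from birth for a six-month fall, and about 7-fold for remaining risk at age 90. The duration-limited figures assume return to pre-pandemic rates and no catch-up. Catch-up would shrink the real effect; a reduction continuing after August 2020 would enlarge it.

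A reader might go further and infer that the life-table calculation is invalid, or that the result is inflated by a fixed large factor at every age. Neither follows. The primary objective is untouched and the equations can stay for this purpose, so this is a should-fix.

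**What to change.** 1. In the Secondary Objective, Impact of COVID-19 Pandemic, Sample table 3 and the captions of Supplementary figures 3 and 4, describe the contrast as a period measure: *lifetime risk if pandemic-period rates persisted for life*. Do not call it the impact of the pandemic.
2. Make the age- and sex-specific incidence rate ratio (pandemic versus pre-pandemic) and the absolute shortfall the main pandemic measure. The shortfall in each band is the pre-pandemic rate × pandemic person-years, minus the observed number. Sample table 2 holds the inputs by age and period; it needs a split by sex, which the change log's sex-specific analysis already requires.
3. If an effect on lifetime risk is wanted, rerun equations 1 to 4 with pandemic rates for a stated duration and pre-pandemic rates otherwise. Present this as a scenario analysis over several durations and degrees of catch-up, not as an upper bound, because rates after 31 August 2020 are not observed.

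The cost is rewording, one split table and, for step 3, a few reruns of the same life table. No new data are needed. The drawback is a less striking pandemic figure.

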***Derivation of variables***

Age will be defined by the age that the patient was on the date of their operative procedure. The number of patients undergoing surgery will be categorised into 5-year age epochs e.g. Age 0-4, 5-9, 10-14…. until 90+. The lifetime risk will be calculated and repeated for consecutive years that we have data available, this has been done in previous papers assessing the lifetime risk of diabetes(9, 10).

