**Supplementary figure 4:** Pre-pandemic (blue line) compared to the pandemic (red line) lifetime risk of first surgery for men and women (Error bars are 95% CIs). The pre-pandemic period was based on data from 2016-19 and the pandemic period was based on data from 2020. This was calculated using the life table method.

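### The pandemic effect is read from a two-period contrast, 2016-19 against 2020, with no check for calendar drift over the roughly 2.3 years between the period midpoints

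*SAP*

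**What the plan says.** The SAP section Impact of COVID-19 Pandemic sets out a causal reading: "We will consider COVID-19 as an exposure and calculate its impact on the lifetime risk of having surgery". The impact is to be investigated by "assessing for any difference in lifetime risk in the specified time-period for pre-pandemic and pandemic". The estimator is a difference between two periods, obtained by "generating the five-year epochs for the pre-pandemic period and then for the pandemic period and comparing the two". A difference counts as statistically significant if the two 95% confidence intervals do not overlap, or if the 95% uncertainty interval for relative change excludes 0. There is also a further test: "The second test will be a T-test, a P-value 0.05 will be considered statistically significant".

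That section names no years. Study design and setting speaks of "comparing data from a pre-pandemic period defined as" and leaves the dates blank, as do the column heads of Sample table 2. The years appear only in Appendix 2, in the captions of Supplementary figures 3 and 4: "The pre-pandemic period was based on data from 2016-19 and the pandemic period was based on data from 2020". Participants and data collection fixes the data window: patients "between 1^st^ April 2015 and 31^st^ August 2020 will be included".

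Derivation of variables adds: "The lifetime risk will be calculated and repeated for consecutive years that we have data available". Nothing in the SAP connects these yearly values to the pandemic contrast.

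**The concern.** A raw difference between two periods equals the impact of the pandemic only if surgery rates in 2020 would otherwise have stayed at their 2016-19 average. The SAP neither states this assumption nor plans to check it. If rates were rising before 2020, the contrast understates a pandemic fall. If they were falling, part of the difference would have arisen without a pandemic.

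The decision rule adds to the problem. It asks only whether the two values differ beyond sampling error, and sampling error is very small in data on a whole nation. A modest drift could therefore be declared significant and reported as an effect of COVID-19.

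Filling in the blank dates would not settle this, because the gap between midpoints remains however exactly the pandemic window is dated.

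**Working it through.** The SAP states no rate, lifetime risk or trend, so there is no figure of its own to reproduce. The check sizes what a drift would do under stated assumptions.

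**1. Gap between midpoints.** Calendar 2016-19 is centred on 1 January 2018 (2018.00). January to August 2020 is centred on about 1 May 2020 (2020.33). The gap is 2020.33 - 2018.00 = 2.33 years. Other readings:

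| Reference period | Pandemic window | Gap (years) |
|---|---|---|
| Calendar 2016-19 | March-August 2020 | 2.42 |
| Calendar 2016-19 | April-August 2020 | 2.46 |
| April 2016-March 2020 | January-August 2020 | 2.08 |
| April 2016-March 2019 | April-August 2020 | 2.71 |

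The range is therefore about 2.1 to 2.7 years. All of 2020 would give 2.50, but the data window rules that out.

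**2. Shift in the rate.** Assume a steady drift g a year and no pandemic effect. The ratio of the 2020 rate to the 2016-19 average is RR = (1+g)^2.33 / mean of (1+g)^k for k = -1.5, -0.5, 0.5, 1.5.

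| g per year | RR |
|---|---|
| -3% | 0.931 |
| -2% | 0.954 |
| -1% | 0.977 |
| +1% | 1.023 |
| +2% | 1.047 |
| +3% | 1.071 |

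The rate moves by about 2% to 7%.

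**3. Shift in lifetime risk.** The cumulative incidence formula in Appendix 2 has the form P = 1 - exp(-H), where H is 5 times the sum of the rates. Under drift it becomes P1 = 1 - (1 - P)^RR. The baselines are assumed.

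- P = 60%, g = -3%: 1 - 0.40^0.931 = 0.574, a shift of -2.6 points.
- P = 60%, g = +1%: 1 - 0.40^1.023 = 0.608, a shift of about +0.85 points.
- P = 40%, g = +1%: 1 - 0.60^1.023 = 0.407, a shift of +0.7 points.
- P = 85%, g = +1%: 1 - 0.15^1.023 = 0.856, a shift of about +0.65 points.

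For assumed baselines of 40% to 85%, the shift is about 0.65 to 0.85 points at 1% a year and 1.9 to 2.6 points at 3% a year. The life table method also allows for death before surgery. With assumed mortality and baselines of 55% to 85% it gave slightly smaller values, 0.6-0.8 and 1.7-2.5 points. Taken together, the range is roughly 0.6 to 2.6 points.

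**4. How small a drift would separate the intervals.** Assume N people in 19 equal age bands, a constant rate and Poisson counts, with T = 4 years for the reference and 8/12 year for the pandemic window. Then SE(P) = (1 - P) × sqrt(95H / (N × T)). For N = 56 million and P = 60%, H = 0.916:

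- Reference: 0.40 × sqrt(95 × 0.916 / 224 million) = 0.025 points.
- Pandemic: 0.40 × sqrt(95 × 0.916 / 37.3 million) = 0.061 points.
- Non-overlap needs 1.96 × (0.025 + 0.061) = 0.17 points, which a drift of about 0.2% a year produces.

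Over N = 10 to 56 million and P = 40% to 80%, the drift needed runs from about 0.15% to 0.6% a year.

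**5. What a contrast with 2019 does.** With the same calendar months the gap is exactly 1 year, so a drift of 1-3% a year shifts the rate by 1-3% instead of 2-7%. At P = 60% and g = -3%, 1 - 0.40^0.97 = 0.589, a shift of -1.1 points instead of -2.6. The bias shrinks but does not vanish.

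**The case against.** The strongest reply is that no bias has been shown. The SAP holds no yearly rate, so the drift could be nil, and a large fall in surgery in 2020 could dwarf it. This stands. A reader might infer that the pandemic result is confounded by calendar time, or that the effect will be overstated or understated. The documents support neither. They show only that the plan does not guard against drift, and every percentage above is conditional on assumed drift, baseline and population.

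Second, the word pooled is not the SAP's. The single 2016-19 reference is read from the captions, and the main text leaves the dates open. This also stands, but the captions are the only place where the periods are given, and they present one reference period.

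Third, the closing aim in Background and rationale is descriptive, and a period comparison serves it. That is fair, but the secondary objective and the analysis section both speak of impact, and the latter of an exposure. The size of the contrast attributed to COVID-19 therefore matters as well as its sign.

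Fourth, the planned yearly values would let a reader see a trend. This holds only in part, because nothing says they will be set beside the contrast or bear on its interpretation.

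Finally, a reader might infer that the primary contrast must become observed against a value projected from the 2016-19 trend. That goes too far. Across 38 strata (19 age bands, 2 sexes) there would be four time points each, and continuing a log-linear trend is itself untestable. With equal variance in each year and in the pandemic window, the projected value has variance 1/4 + 2.33²/5 = 1.34 against 0.25 for the mean. Its standard error is sqrt(1.34/0.25) = 2.3 times as large, and that of the contrast sqrt(2.34/1.25) = 1.4 times. A projection belongs among the sensitivity analyses.

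**Conclusion.** The point holds as a gap in the planned contrast. As written, the SAP counts any change in surgery rates over about 2.3 years (2.1 to 2.7 on other readings) as the impact of COVID-19, and it makes no use of the yearly estimates that would reveal such a change. Whether a drift exists, and in which direction, cannot be told from the document. The illustrative size, roughly 0.6 to 2.6 percentage points of lifetime risk, rests on an assumed drift of 1-3% a year and assumed baselines of 40% to 85%. The finding that a drift well under 1% a year could separate the intervals rests on Poisson counts in an assumed 10 to 56 million people. The point concerns the secondary objective only and should be corrected before the contrast is interpreted.

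**What to change.** In Impact of COVID-19 Pandemic:

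- Show lifetime risk for 2016, 2017, 2018 and 2019 separately beside the pandemic estimate.
- Add a contrast of the pandemic window with the same calendar months of 2019 alone.
- State that a difference will be attributed to the pandemic only if it clearly exceeds the year-to-year drift seen in 2016-19.
- Optionally, add as a sensitivity analysis a contrast with a value projected from the 2016-19 trend. Fix in advance whether slopes are shared or stratum-specific, how overdispersion is handled, and whether the mortality inputs to equation 1 are projected or observed.

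Keep pooled 2016-19 for the primary objective.

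The cost is small. No new data are needed, since the window opens on 1 April 2015. Sample table 2 has two period columns and would need yearly ones. The intervals widen: with equal variance in each year's matching months, the 2019-only contrast has a standard error sqrt(2/1.25) = 1.3 times that of the contrast with the four-year mean, and the projected contrast about 1.4 times. With national counts that is affordable.
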